## Abstract

**Introduction:**

The incidence of renal tumours is increasing and anatomic imaging cannot reliably distinguish benign tumours from renal cell carcinoma. Up to 30% of renal tumours are benign, with oncocytomas the most common type. Biopsy has not been routinely adopted in many centres due to concerns surrounding non-diagnostic rate, bleeding and tumour seeding. As a result, benign masses are often unnecessarily surgically resected. ^99m^Tc-sestamibi SPECT/CT has shown high diagnostic accuracy for benign renal oncocytomas and other oncocytic renal neoplasms of low malignant potential in single-centre studies. The primary aim of MULTI-MIBI is to assess feasibility of a multicentre study of ^99m^Tc-sestamibi SPECT/CT against a reference standard of histopathology from surgical resection or biopsy. Secondary aims of the study include obtaining estimates of ^99m^Tc-sestamibi SPECT/CT sensitivity and specificity and to inform the design and conduct of a future definitive trial.

**Methods and analysis:**

A feasibility prospective multicentre study of participants with indeterminate, clinical T1 renal tumours to undergo ^99m^Tc-sestamibi SPECT/CT (index test) compared with histopathology from biopsy or surgical resection (reference test). Interpretation of the index and reference tests will be blinded to the results of the other. Recruitment rate as well as estimates of sensitivity, specificity, positive and negative predictive value will be reported. Semistructured interviews with patients and clinicians will provide qualitative data to inform onward trial design and delivery. Training materials for ^99m^Tc-sestamibi SPECT/CT interpretation will be developed, assessed and optimised. Early health economic modelling using a decision analytic approach for different diagnostic strategies will be performed to understand the potential cost-effectiveness of ^99m^Tc-sestamibi SPECT/CT.

**Ethics and dissemination:**

Ethical approval has been granted (UK HRA REC 20/YH/0279) protocol V.5.0 dated 21/6/2022. Study outputs will be presented and published nationally and internationally.

**Trial registration number:**

ISRCTN12572202.

Strengths and limitations of this studyMULTI-MIBI is the first multicentre prospective study to assess ^99m^Tc-sestamibi SPECT/CT in the evaluation of indeterminate renal tumours.A composite reference standard of biopsy or surgical pathology allows generalisability of results to patients unwilling or unable to undergo surgical resection.Blinding of clinicians interpreting index and reference tests reduces risk of bias.Possible study limitations include the risk of non-diagnostic renal tumour biopsies and tumour misclassification on biopsy.If the primary outcome (successful recruitment) is met, this will inform a large-scale multicentre study.

## Introduction

The widespread use of cross-sectional imaging has led to an increase in the incidental detection of renal tumours.^1^ Based on data from surgical series, it is estimated that up to 30% of renal tumours are benign,^2^ with an increasing prevalence of benign histology with decreasing tumour size.^3^ The most common type of benign tumour is the oncocytoma. Unlike renal cell carcinoma (RCC), which commonly requires treatment, renal oncocytomas can be safely managed expectantly.^4–6^ However, a critical challenge lies in the identification of benign renal tumours, as traditional anatomic imaging techniques such as ultrasound, CT and MRI are unable to reliably distinguish between the various renal tumour histologies. Although renal mass biopsy can help in this regards, the relatively high non-diagnostic rate (~15%) and associated risk of complications with this procedure have led to its limited adoption in clinical practice.^7 8^ Thus, the majority of patients presenting with an incidental renal mass undergo treatment for a presumed cancer, exposing those with benign tumours to unnecessary surgical risk while consuming significant health resources.^9^

Investigation of new imaging approaches to improve characterisation of incidentally detected small renal masses has been identified as a priority research need by the Renal Cancer Gap Analysis Collaborative, a group composed of clinicians, researchers, patients and caregivers.^10^ In recent years, ^99m^Tc-sestamibi SPECT/CT has emerged as a promising non-invasive tool for the identification of benign renal oncocytomas. ^99m^Tc-sestamibi is a lipophilic cationic radiopharmaceutical that readily accumulates in cells with high concentrations of mitochondria, such as renal oncocytomas.^11^ Conversely, most histologic subtypes of RCC are relatively devoid of mitochondria and express membrane multidrug resistance pumps, which are known to actively export ^99m^Tc-sestamibi out of cells.^11^ These biological differences result in oncocytomas appearing avid, or ‘hot’ and RCCs non-avid or ‘cold’ on MIBI-kidney studies. A systematic review and meta-analysis including 117 renal lesions from single-centre studies showed pooled sensitivity and specificity of MIBI-kidney to detect renal oncocytomas versus other renal lesions was 92% (95% CI 72% to 98%) and 88% (95% CI 79% to 94%), respectively.^12^ No previous trials of MIBI-kidney have been conducted in the United Kingdom (UK), and there have been no multicentre trials.

One potential limitation of ^99m^Tc-sestambi SPECT/CT imaging of renal tumours is that a subset of RCCs exhibits relatively high intracellular concentrations of mitochondria and, therefore, display uptake of the radiotracer.^13–15^ These tumours include the chromophobe subtype of RCC and other oncocytic/chromophobe RCC.^16^ It is reassuring to note that these tumours exhibit generally indolent behaviour and low metastatic potential with excellent outcomes on active surveillance.^17^ We, therefore, termed this group of tumours as oncocytic renal neoplasms of low malignant potential and suggest that with few exception identification of such cT1 tumours on ^99m^Tc-sestamibi SPECT/CT should be managed similarly to that of benign renal oncocytomas.

Given the excellent performance characteristics of ^99m^Tc-sestamibi SPECT/CT for the non-invasive identification of renal oncocytomas and oncocytic renal neoplasms of low malignant potential, there is interest in utilising this test within the UK National Health System (NHS). However, the literature on ^99m^Tc-sestamibi SPECT/CT remains limited to single centres reporting relatively few tumours. We have recently reported on a pump-priming pilot study in the UK.^18^ Herein, we present the protocol for our feasibility study with the following aims^1^: to evaluate the feasibility of a large scale, UK-based, multicentre, clinical trial of ^99m^Tc-sestamibi SPECT/CT in the diagnostic pathway for renal tumours and^2^ to obtain estimates of sensitivity and specificity with which to power a larger scale trial.

## Methods and analysis

Study methods are reported with reference to Standard Protocol Items: Recommendations for Interventional Trials Checklist (SPIRIT)^19^ and SPIRIT-Path extension for cellular and molecular pathology content in clinical trial protocols.^20^

### Study design

A prospective, multicentre study to assess the feasibility and diagnostic performance characteristics of ^99m^TC-sestamibi SPECT/CT in adults (n=50) with solid, enhancing clinical renal tumours (2–7 cm) on cross-sectional imaging. The study design is summarised in figure 1.

**Figure 1 F1:**
[figure not shown]
Study flow diagram.

### Objectives and outcomes

The primary aim of the study is to evaluate whether a multicentre diagnostic test evaluation study of ^99m^Tc-sestamibi SPECT/CT can recruit successfully. Secondary aims are to assess patient and clinician acceptability, refine inclusion/exclusion criteria, sample size requirements and determine clinician training needs for ^99m^Tc-sestamibi SPECT/CT interpretation.

The study objectives are to determine:

Will patients consent to have a ^99m^Tc-sestamibi SPECT/CT prior to surgery or biopsy, including those from under-represented and underserved groups?What factors influence patient’s decisions to participate?What are the perceptions of clinicians and patients of ^99m^Tc-sestamibi SPECT/CT?What barriers and facilitators are there for adoption of ^99m^Tc-sestamibi SPECT/CT?What is the potential cost-effectiveness of using ^99m^Tc-sestamibi SPECT/CT within the NHS?What are the minimally acceptable criteria (MAC) for the sensitivity and specificity of ^99m^Tc-sestamibi SPECT/CT?Is it feasible to train nuclear medicine clinicians across the UK, including those serving under-represented and underserved communities, to interpret ^99m^Tc-sestamibi SPECT/CT?

The study outcomes are as follows:

Primary outcome

Recruitment rate.

Secondary outcomes

Sensitivity and specificity of MIBI to detect benign lesions in this study.Define the MAC for MIBI-kidney to be adopted in clinical practice, to inform the design and parameters of the future definitive clinical trial.Interobserver variability and training requirements in the interpretation of MIBI-kidney (local and central reports will be compared).Patient and clinician perceptions of utility and experience of MIBI-kidney scans and training.The evidence requirements for a cost-effectiveness analysis.

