### Sample size and recruitment

The aim of this study is to assess the feasibility of a multicentre study of ^99m^TC-sestamibi SPECT/CT in the diagnostic pathway for renal tumours. Data from the feasibility phase will be used to inform the design and sample size of the definitive trial. We will aim to recruit 50 patients from 3–6 centres. This sample size will allow us to assess if 80% (95% CI 70% to 90%) of approached patients agree to undergo the study scan. Additionally, this sample size will have sufficient power to detect if there is a significant difference in the estimates of sensitivity between our study population and those reported in the literature. A sample size of 40 patients would achieve 81% power to detect a sensitivity of 0.65 (representing an estimate outside the lower end of the 95% CI for sensitivity from the literature) using a two-sided binomial test at the 5% two-sided alpha level. A 20% inflation to 50 patients, will allow for possible dropouts and other methodological challenges.

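### The accuracy outcome targets benign lesions, but the literature sensitivity it is set against is for oncocytoma only, so the comparison is not like for like and leans downward

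*Protocol article*

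**What the plan says.** Three groupings of histology appear in the protocol article.

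- **Any benign lesion.** The first secondary outcome under Objectives and outcomes is "Sensitivity and specificity of MIBI to detect benign lesions in this study".
- **Oncocytoma only.** The Introduction reports a meta-analysis of 117 lesions: "pooled sensitivity and specificity of MIBI-kidney to detect renal oncocytomas versus other renal lesions was 92% (95% CI 72% to 98%) and 88" per cent for specificity (95% CI 79% to 94%). No other literature sensitivity is given.
- **Oncocytoma plus low-malignant-potential oncocytic tumours.** The Introduction bases interest in the test on "non-invasive identification of renal oncocytomas and oncocytic renal neoplasms of low malignant potential". Of the added tumours it says "These tumours include the chromophobe subtype of RCC and other oncocytic/chromophobe RCC", and it suggests that with few exceptions they "should be managed similarly to that of benign renal oncocytomas".

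Sample size and recruitment then says that the study can detect a "significant difference in the estimates of sensitivity between our study population and those reported in the literature". It uses 0.65 as the alternative, chosen because it lies below the literature interval.

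Study of diagnostic accuracy fixes the index-test side of the 2×2 tables (avid or non-avid; uptake ratio above 0.6 or not). It plans sensitivity, specificity and predictive values with 95% CIs, and the prevalence of oncocytoma and other subtypes. It does not restate which histologies count as reference-positive.

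**The concern.** Sensitivity is a property of a test for a stated target condition. Here the benchmark and the outcome have different targets. A benign tumour that is not an oncocytoma and is cold on the scan counts as a correct negative in the literature figure and as a false negative in the study outcome. The study figure is pulled down by definition, whatever the scan does.

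The third grouping mainly affects the other margin. An avid chromophobe carcinoma is a false positive for benign lesions and for oncocytoma, but a correct positive for the group that the Introduction describes as the useful one.

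The estimates are meant for use. The Introduction makes sensitivity and specificity for powering the larger trial one of two aims. Minimally acceptable criteria are a secondary outcome, and the economic model takes evidence from the trial. If the target is settled only after scans and histology are linked, there are three sets of results to choose from.

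**Working it through.** **The plan's own figure.** The stated power is 81% with 40 patients at a sensitivity of 0.65, by a two-sided 5% binomial test. The null value is not printed. Taking 0.92 as the null and all 40 as target-positive, the exact test rejects at 32 or fewer (lower-tail probability 0.0127), and power at 0.65 is 98.8%, so 81% is not reproduced. It appears with 18 target-positives (81.1%), an input that the article does not state. The inflation does reproduce: 40/(1 − 0.20) = 50. The power figure is a separate matter; what follows does not depend on it.

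**Inputs from the Introduction.** Sensitivity in oncocytoma is 0.92. Avid share among non-oncocytomas is 1 − 0.88 = 0.12. At most 30% of tumours are benign, so at most 0.30 × 40 = 12 benign lesions.

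**Assumed inputs (not in the article).** *f* is the oncocytoma share of benign tumours, taken as 70%, 80% and 90%. *u* is the avid share of other benign tumours, taken as 0 to 0.12.

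**Expected sensitivity for benign lesions** = 0.92*f* + *u*(1 − *f*). This is below 0.92 whenever *f* < 1 and *u* < 0.92, so the direction does not depend on the assumed values.

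**Rejection of 0.92 with 12 benign lesions.** At 0.92, P(X ≤ 8) = 0.0120 and P(X ≤ 9) = 0.065, so the exact test at 2.5% per tail rejects at 8 or fewer. It cannot reject upward, since 0.92^12 = 0.37.

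| *f* | *u* | Expected sensitivity | P(X ≤ 8) |
|---|---|---|---|
| 0.70 | 0 | 0.644 | 0.6694 |
| 0.70 | 0.12 | 0.680 | 0.5681 |
| 0.80 | 0 | 0.736 | 0.3949 |
| 0.80 | 0.12 | 0.760 | 0.3205 |
| 0.90 | 0 | 0.828 | 0.1368 |
| 0.90 | 0.12 | 0.840 | 0.1114 |
| 1.00 | any | 0.920 | 0.0120 |

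**Where the benchmarks are crossed.** Expected sensitivity equals 0.65 at *f* = (0.65 − 0.12)/0.80 = 0.66 for *u* = 0.12, and at 0.65/0.92 = 0.71 for *u* = 0. It equals the lower literature limit, 0.72, at *f* = 0.75 and 0.78 respectively.

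**If uptake in other benign tumours is higher.** With *u* = 0.21 (1 − 0.79, from the lower limit for specificity), expected sensitivity at 70%, 80% and 90% is 0.71, 0.78 and 0.85.

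**Specificity.** With 12 benign lesions among 40, one avid chromophobe tumour costs 1/28 = 3.6 points for benign lesions. With about 8 oncocytomas (0.70 × 12 = 8.4) it costs 1/32 = 3.1 points for oncocytoma. In the third grouping it is a true positive.

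**The case against.** Several points limit what can be claimed, and most of them stand.

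- A reader might infer that the plan analyses three rival target conditions. It does not. The only accuracy outcome is for benign lesions, and the analysis and health-economics sections also frame the decision as benign against malignant. The low-malignant-potential grouping is confined to the abstract and Introduction.
- A reader might infer that a scan performing as published would be declared a failure. The article does not say so. The accuracy analysis lists estimates with intervals and no test against the literature; the comparison is stated only in the sample-size section. The value 0.65 is an alternative for power, not a stop or go threshold, and the primary outcome is recruitment rate.
- The size depends on two inputs that the article does not give. At an 80% share, expected sensitivity is still inside the literature interval; at 90% the effect is modest.
- A reader might infer that oncocytoma must become the sole main definition. That does not follow. A cold benign tumour sent to surgery is a real miss in the pathways being modelled, so a lower sensitivity for benign lesions can be true information.
- Histology is reported by WHO subtype with central review, so every table can be built from planned data. A detailed histology list may properly sit in an analysis plan that is not shown.

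None of this removes the mismatch, which is printed in the article and is not an omission. Even without a formal test, setting the study estimate beside 92% compares answers to two different questions.

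**Conclusion.** The point holds as an inconsistency between the stated accuracy outcome and the literature value that the sample-size section sets against it. The bias is downward whenever some benign tumours are not oncocytomas and take up tracer less often than oncocytomas do. The article's own statements support both conditions: it calls oncocytoma only the commonest benign type, and pooled specificity is 88%.

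The size is uncertain. Over assumed shares of 70% to 90% and uptake of 0 to 12%, expected sensitivity runs from 0.64 to 0.84 in place of 0.92. The chance of a spurious difference with 12 benign lesions runs from 67% down to 11%. If nearly all benign tumours are oncocytomas, it is negligible.

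This should be fixed, but it does not threaten the feasibility question. What is at risk is a misleading accuracy figure carried into the definitive trial, the minimally acceptable criteria and the economic model.

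**What to change.** Before index and reference results are linked:

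1. Make any comparison with the literature on oncocytoma versus all other lesions only, and say so in Objectives and outcomes and in Sample size and recruitment.
2. In Study of diagnostic accuracy, prespecify separate 2×2 tables for (a) oncocytoma, (b) any benign lesion, and (c) oncocytoma plus low-malignant-potential oncocytic neoplasms, each with a closed histology list.
3. State which table gives the main estimate passed to the economic model and the definitive trial. Any benign lesion may remain the main clinical target.

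The cost is some rewording and two extra tables from data already collected. There is one real loss: the literature comparison rests on fewer positives. At a 70% share, 12 benign lesions become about 8 oncocytomas. The exact test then rejects at 5 or fewer (lower-tail probability 0.021), and power at 0.65 is about 57%, against 65% with 12.

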### Study setting

The study will be conducted in 3–6 NHS hospitals in England.

### Eligibility criteria

Consecutive patients discussed at specialist multidisciplinary team meetings will be screened for eligibility over a planned 15-month recruitment period. The inclusion criteria for entry to the study are adult patients (≥18 years) of any gender with a clinical T1 indeterminate solid renal tumour (2–7 cm) on cross-sectional imaging, willing and able to provide informed consent. Patients will be required to have surgery or renal tumour biopsy planned as part of their standard clinical care. Patients entering watchful waiting or active surveillance pathways without histologic diagnosis will be excluded. Other exclusion criteria will include cystic tumours, pregnant and breastfeeding patients, those with a known allergy to ^99m^Tc-sestamibi and those unwilling or unable to undergo the study procedures.

### Test methods

#### Index test

Nuclear medicine clinicians involved in the study will receive study-specific training on the interpretation of ^99m^Tc-sestamibi SPECT/CT from international experts at the beginning of the recruitment period. The training will include a lecture on ^99m^Tc-sestamibi SPECT/CT principles, ‘hands-on training’ supported by experienced faculty and a precourse and postcourse assessment.

900 MBq of ^99m^Tc-sestamibi will be injected intravenously in a single bolus, 75 min before SPECT/CT acquisition of the abdomen with the superior extent of the field-of-view set to the top of the liver dome. CT and SPECT image acquisition will follow manufacturer instructions and local experience. At minimum, we suggest that participating centres have SPECT/CT systems with the following specifications: at least two-slice helical diagnostic CT scanner, available low-energy all-purpose or low-energy high-resolution collimator, gamma camera or digital detector elements appropriate for 140-kEv photopeak acquisition and manufacturer-derived iterative reconstruction that includes scatter and attenuation correction.

The reporting clinician will document a qualitative assessment of the tumour as avid, non-avid or indeterminate on reconstructed SPECT/CT images, blinded to clinical information and the result of the histopathology reference test. A spherical region of interest will be drawn to measure maximum uptake in attenuation-corrected images within (a) the tumour and (b) the ipsilateral renal parenchyma. A ratio of maximum uptake between the tumour and normal renal parenchyma will be calculated. All ^99m^TC-sestamibi SPECT/CT scans will be transferred for central review at the lead site (Royal Free Hospital) and discordant reports resolved by discussion and consensus. Local site clinicians will report a subset of studies a second time at the end of the recruitment period to allow assessment of intrarater reliability.

#### Reference test

Histopathology from the final surgical resection specimen is considered the ‘gold standard’ diagnostic test to determine renal tumour subtype. It is worth noting that although biopsy allows for histological diagnosis, questions remain about the accuracy of this technique for determining the precise histology of a renal tumour, mostly relating to an approximately 15% non-diagnostic rate of this procedure^7 8^ and the need for architectural findings in the tissue sample to definitively diagnose some tumour types.^21^ Despite this, we feel a composite reference standard of surgery and biopsy allows generalisability of the results to non-surgical populations. To maximise the accuracy of this procedure, tumour biopsy will be performed using an image-guided approach by an interventional radiologist experienced in the technique. In the case of a non-diagnostic biopsy, the patient will be offered a second attempt, according to local guidelines.

Histopathological reporting of both biopsy and surgical samples will be performed by qualified pathologists at collaborating sites in accordance with the current WHO classification system for renal tumours,^16^ as per standard care. Pathologists will be blinded to the ^99m^Tc-sestamibi SPECT/CT result. Pathology slides/images will be exported for central review by a specialist uro-oncology pathologist and archiving at the lead site (Royal Free Hospital).

### Sample size and recruitment

The aim of this study is to assess the feasibility of a multicentre study of ^99m^TC-sestamibi SPECT/CT in the diagnostic pathway for renal tumours. Data from the feasibility phase will be used to inform the design and sample size of the definitive trial. We will aim to recruit 50 patients from 3–6 centres. This sample size will allow us to assess if 80% (95% CI 70% to 90%) of approached patients agree to undergo the study scan. Additionally, this sample size will have sufficient power to detect if there is a significant difference in the estimates of sensitivity between our study population and those reported in the literature. A sample size of 40 patients would achieve 81% power to detect a sensitivity of 0.65 (representing an estimate outside the lower end of the 95% CI for sensitivity from the literature) using a two-sided binomial test at the 5% two-sided alpha level. A 20% inflation to 50 patients, will allow for possible dropouts and other methodological challenges.

